## Description of protocol

### Aims

The primary aim of the present study is to explore whether the 16 weeks therapy model with clomiphene citrate (CC) leads to stimulation of endogenous luteinizing hormone (LH) and testosterone production, if the treatment model is safe, and if the model is more effective in reducing AAS withdrawal symptoms compared to no intervention. The secondary aims are to detect health risks during ongoing AAS use in the intervention group only and assess whether and to what extent the health risks are reduced 12 months after cessation of AAS.

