**Inclusion criteria**		
Age	≥18 years	≥18 years
AAS use	Continuous AAS use ≥6months	Cycle, ≥6weeks between cycles
Dose	Supraphysiological	≥400 mg/week
AAS dependence	3 or more items last 12 months: tolerance, withdrawal, increased amount, unsuccessful efforts to reduce or cease use, ↑time to obtain/use substances, ↓social/recreational/occupational activities due to use, continued AAS use despite mental and/or physical side effects	No
Plan to cease AAS use	Wish to cease use, previous unsuccessful attempts	No
SUD treatment	Being enrolled in or referred to Substance Use Disorder (SUD) treatment	No
Hormonal and liver status at intervention start	Serum testosterone < 25 nmol/l, liver enzymes alanine transaminase (ALT) and aspartate transaminase (AST) < 3 x upper limit of normal range (ULN) (normal range ALT 10–70 U/L, AST 15–45 U/L)	No

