### Outcomes and instruments

Primary outcomes:(1)*Changes in self-reported symptoms of hypogonadism,* mental health state, and symptoms associated with AAS use. The following will be assessed for both the intervention and comparison group: fatigue, depression, suicidal ideation, anxiety, wellbeing, sexual dysfunction, sleep quality, aggression, and body dysmorphia.(2)*Side effects related to CC* will be specifically evaluated for the intervention group.

Secondary outcomes:

Change in measures of physical health from baseline to follow-up for the intervention group:•Weight, body mass index (BMI), degree of striae, acne, androgen alopecia and gynecomastia•Endocrine status, metabolic status, liver and kidney function (blood tests)•Cardiovascular status: Blood pressure, electrocardiogram (ECG), vascular morphology (carotid intima-media thickness and pulse wave velocity) and -function (flow-mediated dilation and carotid artery reactivity)•Body composition; total fat mass, visceral and subcutaneous fat tissue, total lean mass, and bone mineral density•Testicular volume and sperm quality•Immunological biomarkers, analyzed from biobanked blood and adipose tissue samples

Change in measures of mental health risks from baseline to follow-up after 12 months:•Depression and anxiety levels, AAS dependence, body image concerns, aggression, AAS use, and adherence to SUD treatment

Study participants included for the intervention will be screened for eligibility at baseline and examined to assess mental health status, comorbidity, AAS history, AAS dependence and SUDs with validated instruments, see flow chart for study events (Table 1).

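### AAS use and AAS dependence are entry criteria as well as 12-month outcomes, so a test of change from baseline says little; report abstinence and remission proportions instead

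*Protocol article*

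**What the plan says.** The secondary aim in the Aims section is to "assess whether and to what extent the health risks are reduced 12 months after cessation of AAS", in the intervention group only. Outcomes and instruments turns this into "Change in measures of mental health risks from baseline to follow-up after 12 months" and lists "Depression and anxiety levels, AAS dependence, body image concerns, aggression, AAS use, and adherence to SUD treatment".

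Table 1 sets the entry criteria for the same men. On use: "Continuous AAS use ≥6months". On dependence: "3 or more items last 12 months", drawn from seven listed items. On motivation: "Wish to cease use, previous unsuccessful attempts". On treatment: "Being enrolled in or referred to Substance Use Disorder (SUD) treatment".

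Three other sections matter here:
- Study design places the baseline assessments before the intervention, while the men are still using AAS.
- The section on self-reported mental health gives 6- and 12-month follow-up to the intervention group only.
- The Data analysis plan sets a two-sided 5% significance level with 95% confidence intervals. It names chi-square and Fisher's exact tests for categorical variables and relies on a per-protocol analysis where data are missing.

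**The concern.** A change from baseline is informative when the baseline could have gone either way. For AAS use and AAS dependence, the eligibility rules fix the baseline. If either is scored as present or absent, every man starts as present, nobody can get worse, and each man who differs at 12 months counts as an improvement. The null hypothesis of no net change then has little interest in men chosen because they use, are dependent and want to stop. No untreated group is followed to 12 months, so nothing separates the effect of the intervention from selection or from stopping that would have happened anyway.

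The risk is a report that use or dependence fell significantly when most men were still using or dependent. The result that matters for planning a later trial is how many men are off AAS at 12 months and how precisely that is known. A p-value against a selected baseline does not give it.

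**Working it through.** The article states no figure for this point, so there is none to reproduce. The check compares the outcomes with the entry criteria and then gives the consequence in numbers.

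**Inputs from the article.** Intervention group of 25–30 (Sample size determination); two-sided alpha of 0.05 (Data analysis plan); entry criteria (Table 1). The article does not give the scoring of use and dependence at 12 months.

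**Possible direction of change.**
- AAS use, yes/no: baseline 100%, so change can only be favourable. As dose or frequency, it can also rise.
- AAS dependence, yes/no: baseline 100%, so change can only be favourable. As an item count, baseline is 3 to 7, and men below 7 can rise.
- SUD adherence: entry requires enrolment or referral, not adherence. If being in treatment were taken as 100% at entry, it could only fall, which is unfavourable.

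**How few changers give significance (yes/no scoring).** With all discordant pairs in one direction, the exact paired two-sided p-value for k changers is 2 × 0.5^k.
- k = 5: 2 × 0.5^5 = 0.0625
- k = 6: 2 × 0.5^6 = 0.031

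Fisher's exact test, which the plan names but which ignores the pairing, has the same threshold. Comparing 0 with 6 changers gives p = 0.022 (n = 25) and 0.024 (n = 30); comparing 0 with 5 gives 0.0502 and 0.052.

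Six changers are:
- 6/25 = 24% (exact 95% CI 9–45%), leaving 76% unchanged
- 6/30 = 20% (exact 95% CI 8–39%), leaving 80% unchanged

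**How often significance would occur.** This is P(X ≥ 6) for X binomial(n, q), where q is the true proportion changing. The article gives no value for q, so these rates are assumptions.

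| q | n = 25 | n = 30 |
|---|---|---|
| 10% | 0.03 | 0.07 |
| 15% | 0.16 | 0.29 |
| 20% | 0.38 | 0.57 |
| 30% | 0.81 | 0.92 |

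**Dependence as an item count.** A simulation used seven items, a personal endorsement probability that is logit-normal (mean 0 or 0.8; SD 0.5, 1.0 or 1.5), entry at three or more items, and a retest with no true change. Across these settings 28–35% of men rose, 38–50% fell, the mean fell by about 0.1–0.5 items, and 6–22% dropped below three. Another set of assumed means and reliabilities (test–retest correlation 0.59–0.74) gave 12–27% below three. The count is therefore not one-way, but it is biased towards reduction by an amount that depends on assumed reliability.

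**The case against.** A reader might infer that three of the listed outcomes can move only one way and that a finding of reduced risk is close to built in. The documents do not support that reading.

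- **SUD adherence does not belong in the argument.** Adherence is not the entry criterion, and any ceiling would work against a favourable result.
- **One-way movement depends on yes/no scoring, which the article does not fix.** A condensed article may leave scoring to the full protocol. This stands, and it limits the claim to status measures. It does not remove the problem for a count, because selection at the threshold still pulls the retest down.
- **Significance is far from assured.** The Background says cessation often ends in restart, and Table 1 selects men whose earlier attempts failed, so low change rates are plausible. At 10% the chance is only 3–7%.
- **The article does not name a paired exact test or say outright that these outcomes will be tested; it allows descriptive statistics where appropriate.** That is fair, but the stated significance rule is general, and the categorical test it does name has the same threshold of six.
- **From a 100% baseline, the change is arithmetically the abstinence or remission proportion, and 95% intervals are already promised.** Also true. What remains is which men are in the denominator, how missing men are counted, and whether a p-value is attached.
- **A dependence look-back that includes the withdrawal weeks would work against apparent remission.** This is correct: withdrawal is one of the seven items. It is a reason to fix the window, not to keep the test.

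**Conclusion.** The point holds for two outcomes, AAS use and AAS dependence. As statuses they are 100% at baseline by selection and can change only favourably. As a dependence count, the measure is pulled downwards by the entry threshold. With no comparator at 12 months, a significant change from baseline cannot be credited to the intervention, and it can be reached with 76–80% of men unchanged. It is favoured by selection, not guaranteed.

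The six-changer threshold rests on yes/no scoring and complete data on 25–30 men. The trial-level probabilities rest on assumed change rates, and the size of the regression effect rests on assumed reliability. SUD adherence raises a separate question of definition: a man who was only referred has no clear baseline adherence from which to compute a change. These are secondary outcomes in a declared pilot, so the matter is one of informative reporting and does not undermine the study.

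**What to change.** - Do not test AAS use or AAS dependence as change from baseline.
- Report the proportion of all enrolled men abstinent from AAS at 12 months, using self-report together with the urine AAS screen already planned at follow-up, with an exact 95% CI.
- Report the proportion of all enrolled men no longer meeting the dependence criterion, with an exact 95% CI, and show the item count descriptively. Score dependence at 12 months over a recent window that does not reach back to the cessation period.
- For both proportions, add a sensitivity analysis that counts missing men as not abstinent or not remitted, so that the result does not rest on per-protocol handling alone.
- Report SUD treatment as the proportion retained at 12 months.
- Keep change from baseline for depression and anxiety, body image concerns and aggression.

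The cost is a change of wording in the outcomes and analysis sections; no new visits or samples are needed. The drawback is that a p-value gives way to a proportion with a wide interval; for 6 of 25 that interval is 9–45%.

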#### Self-reported mental health, well-being and AAS withdrawal symptoms

To investigate mental health state, wellbeing and AAS-withdrawal symptoms after AAS cessation, the following self-reporting questionnaires will be administered via a web-app every second week for 16 weeks for both groups and at follow-up at 6 and 12 months for the intervention group: Hopkins Symptom Checklist-10 (HSCL-10) to evaluate psychological distress, suicidal ideation item from Montgomery and Åsberg Rating Scale (MADRS), items from Health-related quality of life (HRQOL) to evaluate sexual function, Shortened Fatigue Questionnaire, WHO-5 Wellbeing Index and Jenkins Sleep Scale (JSS), Body Perception Questionnaire; and Visual Analog Scale (VAS) to measure aggression, cognitive function, body image and pain. Treatment satisfaction will be assessed using VAS for the intervention group only.

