## Background

Non-prescribed AAS are predominantly utilized by male recreational athletes in cyclic patterns, with intermittent breaks or continuous administration. Global lifetime prevalence of AAS use among men is estimated to be 6.4 %, but is found higher in subpopulations [1] and associated health risks and behavioral outcomes make AAS use a public health concern [2]. The wide range of adverse effects on mental [3] and physical health [[4], [5], [6]] includes negative effects on the cardiovascular system such as ventricular dysfunction [7], myocardial hypertrophy [8], hypertension [9], severe biventricular cardiomyopathy [10], acute myocardial infarction and sudden cardiac death [8,11]. Increased carotid intima-media thickness, reduced arterial elasticity and lower carotid artery compliance are early predictors of atherosclerosis and cardiovascular risk that are found among men with long term AAS use [12]. AAS use is also associated with altered renal, hepatic and metabolic functions [13]. High androgen levels might lead to gynecomastia and several dermatological conditions, and infertility during ongoing use is common due to the disruption of hypothalamic-pituitary-gonadal (HPG) axis [14,15].

One in three people using AAS seem to develop a dependence syndrome characterized by a pattern of escalating doses and reduced breaks between cycles, or continuous use despite experiencing adverse effects and a desire to cease use [16]. The neuroendocrine mechanism of AAS dependence is linked to suppression of the hypothalamic-pituitary-gonadal (HPG) axis leading to AAS-induced hypogonadism (ASIH) [14]. The features of androgen deficiency (fatigue, depression, anxiety, and sexual dysfunction) will first occur weeks after AAS cessation. The endogenous testosterone production typically recovers after 3–12 months, but this phase is hard to endure [17], often resulting in restart of AAS use.

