## Methods and analysis

In this open-labeled non-randomized proof-of-concept intervention study, we aim to include 25–30 AAS-dependent men who struggle to cease their AAS use. The subjects in the intervention group will receive 25 mg chlomiphene citrate every second day following AAS cessation for 16 weeks. The comparison group comprise participants in another study of men who ended AAS use temporarily without the intervention and the groups will be compared on self-reported withdrawal symptoms.

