### Study design

The study includes two sub-studies with

A) *Within-subjects repeated measures design* to monitor the intervention group with physical and mental health parameters and blood sampling prior to intervention start and while still using AAS, during 16 weeks of intervention, and at follow-up at 6 and 12 months (Table 2).

**Table 2 tbl0002:** Flow chart of study events during the study period for the intervention group, modified version of SPIRIT.

B) *Single center – single group – case-comparison design*:

Male participants with AAS dependence and continuous AAS use with the intention to cease use permanently comprise the intervention group. The data from the intervention group will be compared with data from an ongoing study of men who intend to cease a cycle of AAS use temporarily without receiving intervention. Participants from both studies will self-report withdrawal symptoms and other subjective health measures during ongoing use and after cessation. The intervention group will self-report withdrawal symptoms every 2 weeks for 16 weeks of intervention, see Fig. 1.

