### Data analysis plan

Data analyses will follow a full analysis set, with a per protocol plan. Descriptive statistics will be used when appropriate and for reported adverse events. For between-group comparisons and to control for the effect of baseline characteristics, we plan to use General Linear Mixed Models (GLMM) with a within subject repeated measures design at baseline, 6 months and 12 months. In cases where the outcomes do not meet the normality assumption, we will apply a General Alinear Mixed Models (GAMM) approach. The results of statistical analyses will be performed using 95 % CIs, and a two-sided P value of < 0.05 will be used to indicate statistical significance. General linear models may be utilized in cases where GLMM/GAMM is considered inappropriate. Two sample *t*-tests will be used for between-group comparisons of numerical variables, when we see no need to adjust for confounding variables. Numerical data not following normal distribution will be presented as medians (25th-75th percentiles), using non-parametric tests such as the Wilcoxon rank sum tests (Mann-Whitney) to compare differences between groups. Chi^2^-tests and Fischer's exact will be applied for categorical variables. Per protocol analysis will be applied in cases of missing data to detect any discrepancy that might affect the robustness of the results. All statistical calculations and analyses will be conducted using up-to-date versions of the statistical software STATA and SPSS.

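### The between-group symptom comparison stops when clomiphene stops, so it can show relief during treatment but not a lasting reduction in withdrawal symptoms

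*Protocol article*

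**What the plan says.** One of the primary aims (Aims) is to explore "if the model is more effective in reducing AAS withdrawal symptoms compared to no intervention". No time window is attached to this aim.

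Methods and analysis gives the regimen as "25 mg chlomiphene citrate every second day following AAS cessation for 16 weeks". Under The intervention, testosterone gel is added for the first four weeks, and hCG is possible from week 4 if the response is poor.

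The questionnaire section gives the symptom schedule as "every second week for 16 weeks for both groups and at follow-up at 6 and 12 months for the intervention group". Study design links those weeks to treatment: "The intervention group will self-report withdrawal symptoms every 2 weeks for 16 weeks of intervention". It also says that both groups report symptoms during ongoing use, so a shared baseline exists.

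The Data analysis plan describes the mixed model for between-group comparisons as one "with a within subject repeated measures design at baseline, 6 months and 12 months".

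On natural history, the Background says that deficiency symptoms "will first occur weeks after AAS cessation" and, on recovery, "The endogenous testosterone production typically recovers after 3–12 months".

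**The concern.** If treatment and the controlled comparison end together, a regimen that prevents withdrawal symptoms and one that only holds them off while it is taken can look the same. The difference matters here because the stated purpose is to restart the men's own testosterone production, and the Background describes the recovery phase as hard to endure and often ending in renewed AAS use.

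Two things follow. First, the comparative aim has no time limit, so a favourable 16-week result could be reported as a reduction in withdrawal symptoms in general. The article also intends its effect sizes to inform later trials, and an on-treatment effect would be passed on without that label. Second, the model times in the Data analysis plan suggest an off-drug comparison between groups, for which the questionnaire section schedules no comparison-group data. Those times also leave out week 16, which is needed to measure any return of symptoms in the treated men.

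**Working it through.** **Inputs**

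- Clomiphene: 16 weeks from cessation (Methods and analysis).
- Symptom reports, both groups: every 2 weeks to week 16 (questionnaire section).
- Symptom reports, treated men only: 6 and 12 months (same section).
- Natural recovery: 3 to 12 months (Background).
- Conversion: 365.25 / 7 = 52.18 weeks per year, or 4.348 weeks per month.

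**Calendar**

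- Shared visits after cessation: 16 / 2 = 8, all within treatment, the last at its end.
- Week 16 in months: 16 / 4.348 = 3.7.
- Natural recovery range in weeks: 52.18 / 4 = 13 to 52.
- 6-month visit: 52.18 / 2 = week 26.1, which is 26.1 − 16 = 10.1 weeks after the last dose.
- 12-month visit: week 52.2, which is 52.2 − 16 = 36.2 weeks after the last dose.
- Off-drug symptom visits: 2 in treated men, 0 in the comparison group, and none in either group between weeks 16 and 26.

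**Schedule against planned model**

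| Time | Treated | Comparison | Named in the mixed model |
|---|---|---|---|
| Baseline | yes | yes | yes |
| Weeks 2 to 16 | yes | yes | no |
| 6 months | yes | no | yes |
| 12 months | yes | no | yes |

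For symptoms, the model as written has only baseline in common between the groups. It leaves out all eight later visits that they share.

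**Illustration (assumed curves, not an estimate)**

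Let the comparison group's excess symptom score be 1 up to week 16 and then fall in a straight line to 0 at week 26. On a two-weekly grid from week 2 to week 52 (26 points) it sums to 8 + 0.8 + 0.6 + 0.4 + 0.2 = 10.

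- Full prevention: the treated score is 0 throughout. Mean contrast to week 16 is 1.0; to week 52 it is 10 / 26 = 0.38.
- Pure postponement: the treated score is 0 to week 16 and then follows the same curve 16 weeks later, again summing to 10. Mean contrast to week 16 is 1.0; to week 52 it is (10 − 10) / 26 = 0.00.

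The 16-week comparison is identical in the two cases. The treated men's score at week 26 is not: 0 under prevention and 1 under postponement. At week 52 it is 0 under both. So the planned 6-month visit can show a rebound of this length, but only against the men's own week-16 value.

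**The case against.** A reader might infer that the comparative aim is unsupported altogether. The document does not bear that out. The aim concerns a 16-week therapy model, is worded as exploration, and sets no durability requirement. A comparison over weeks 0 to 16 does address symptoms during that model, within the limits of a non-randomised design that the article admits. Only a claim of lasting benefit lacks a comparator.

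A reader might also infer that the study sees nothing after week 16. It does: treated men have symptom scores and sex hormones at 6 and 12 months, and urine is screened for AAS at follow-up. This evidence is uncontrolled, misses weeks 16 to 26, and could be masked by testosterone replacement or resumed AAS use.

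Nor does the provision for men with a poor hormonal response and severe symptoms after 16 weeks show that rebound is expected. It describes non-response at the end of treatment, not relapse after an effective drug is withdrawn.

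The roughly 36 weeks without comparator data are not a measure of bias either. Comparison men stop only temporarily, with at least 6 weeks between cycles, so some may restart AAS before or soon after week 16. Later data from them might not represent untreated withdrawal. The same applies to part of the 16-week window.

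Finally, naming a single contrast is often left to the analysis plan. That is fair for the persistence check taken alone. But the article does state the model times, and those it states do not fit its own questionnaire schedule.

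**Conclusion.** The point holds in limited form. On the text schedule there are eight shared symptom visits after cessation, all on treatment, and none off it. The between-group result can support relief during the 16-week treatment period and no more. Evidence on persistence comes only from treated men, at about 10 and 36 weeks off drug. The model times in the Data analysis plan and the schedule in the questionnaire section disagree for the symptom outcomes and must be reconciled.

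No numerical bias is claimed: the illustration shows that two different effects can give the same 16-week result, not how likely either is.

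Assumptions: the text schedule is complete (the timeline figure and the flow chart of study events were not available), clomiphene starts at cessation, and the 6- and 12-month visits are counted from cessation. Each week of delay before the first dose would shorten the off-drug intervals by a week. This is an inexpensive improvement to an exploratory pilot, not a flaw that invalidates it.

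**What to change.** 1. **Aims:** limit the comparative aim to withdrawal symptoms during the 16-week treatment period.
2. **Data analysis plan:** for symptom outcomes, place the between-group model on baseline and the two-weekly visits to week 16, and reconcile this with the questionnaire section. Keep 6 and 12 months for within-group analyses of the treated men.
3. **Persistence check:** state the treated men's within-man change from week 16 to 6 months and to 12 months. Report it beside the 16-week comparison, with the numbers who received testosterone replacement or resumed AAS.
4. **Interpretation:** if symptoms return, keep the on-treatment result and make no claim of sustained benefit. If they do not return, say that this alone does not prove prevention, because natural recovery, replacement therapy or resumed AAS use could explain it.

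Cost: no new data, a narrower efficacy claim, and one extra uncontrolled contrast. Following the comparison group beyond week 16 would be the fuller remedy, but it would help only for men still off AAS, and they may be few.
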